### Statistical analysis

Demographic characteristics, such as weight, height and body mass index, will be presented as the mean and standard deviation. Median, maximum and minimum values will be used to describe poststroke time and UE-FMA score.

For all dependent variables, normality (Kolmogorov-Smirnov) and homogeneity (Levene) tests will be applied. If the variables present a normal and homogeneous distribution, then two-way analysis of variance with repeated measurements and Bonferroni’s correction will be used to examine the effect of group-by-evaluation time interaction, group (AE + m-CIMT and Stretching + m-CIMT), and evaluation time (baseline, 3, 30 and 90 days after the intervention). To protect against Type I error, Bonferroni’s correction will be used. Thus, each of the 10 planned comparisons will have to achieve *p* = 0.005 for statistical significance. The partial eta squared (η^2^) will be used to determine the effect size of the intervention. The mean difference from pre- and post-interventions and the corresponding 95% confidence interval (95% CI) will be calculated for each group (EA + m-CIMT and Stretching + m-CIMT) in order to estimate the effect of the intervention.

Otherwise, the Friedman test (*p* < 0.05) will be used followed by the Wilcoxon test with Bonferroni’s adjustment (*p* < 0.008) to compare evaluation time for each group baseline, 3 days, 30 days, 90 days after the end of treatment. The Mann-Whitney test with Bonferroni’s adjustment (*p* < 0.012) will be used to compare the groups in each time evaluation (EA + m-CIMT and Stretching + m-CIMT).

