**Methods:**

Sixty-two individuals with chronic hemiparesis will be randomized into two groups: Aerobic exercise + m-CIMT or Stretching + m-CIMT. m-CIMT includes 1) restraint of the nonparetic upper limb for 90% of waking hours, 2) intensive task-oriented training of the paretic upper limb for 3 h/day for 10 days and 3) behavior interventions for improving treatment adherence. Aerobic exercise will be conducted on a stationary bicycle at intervals of moderate to high intensity. Participants will be evaluated at baseline, 3, 30, and 90 days postintervention by the following instruments: Motor Activity Log, Nottingham Sensory Assessment, Wolf Motor Function Test, Box and Block Test, Nine-Hole Peg Test, Stroke Specific Quality of Life Scale and three-dimensional kinematics. The data will be tested for normality and homogeneity. Parametric data will be analyzed by two-way ANOVA with repeated measures and Bonferroni’s adjustment. For nonparametric data, the Friedman test followed by the Wilcoxon test with Bonferroni’s adjustment will be used to compare the ratings for each group. To compare the groups in each assessment, the Mann-Whitney test will be used.

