### Sample size

The sample size was calculated with G*Power software using the independent t-test, 85% power, alpha 0.05, and 20% drop-out. Data from the Nine-Hole Peg test proposed by Yoon et al. (2014) [29] were considered for this calculation. Thus, a sample size of 78 individuals (39 per group) is required for this study (Fig. 1). However, after collecting the first five participants per group, the sample size will be recalculated for the same variable.

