### Randomization and blinding

The randomization method will be matched by age and gender at 1:1 per-muted block randomization generation by a web-based randomization tool (www.random.org). This sequence will be performed independently and remotely by a blinded investigator who will not have contact with other research procedures. Randomization will be concealed until group allocation.

Participants will not be identified by their real names and will not be aware of which study arm they allocated. Thus, the assessors will also be blind, as they will identify the patients by codes and will not have contact with other research procedures. The same standards will be applied to the staff responsible for following the m-CIMT procedures. Data analysis will be conducted by a researcher who is not involved in any stage of recruitment, screening, assessment, or intervention.

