### Study setting and recruitment

Potential participants will be identified from the health information contained in the medical reports of the School Health Unit and Basic Health Units of the University Hospital, Santa Casa in São Carlos and from the local community using advertisements such as posters and pamphlets.

Potential participants will be screened to determine if they meet eligibility criteria (Table 1), participate in the process of informed consent, and then an initial assessment will be conducted to collect data regarding the sample characterization. The screening, consent and initial assessment will perform in a single day at the individual’s home to ease the burden on participants for transportation. This screening will include a brief medical history and physical examination to verify the eligibility criteria of the individuals. Subsequently, eligible individuals will undergo evaluation of the sensorimotor and cardiopulmonary measures.

Participants will be evaluated on study outcome measures at four time points: baseline, 3 days, 30 days, and 90 days after completion of the protocol. All evaluations will be conducted across two days, with a minimum interval of 24 h and a maximum of 3 days between evaluation days.

Participant screening will include medical history, Mini-Mental Status Examination, physical examination (anthropometric data), active and passive range of motion assessment using goniometer and the questionnaire of the use of the affected upper extremity *Motor Activity Log* (MAL). Moreover, muscle tone assessment by Modified Ashworth Scale [31, 32], upper extremity sensorimotor impairment assessment using Fugl-Meyer Assessment (UE-FMA) [33], Manual preference will be assessed by the Edinburgh Handedness Inventory [34], considering hand preference before the stroke. After screening, if the individuals meet the inclusion criteria, then they will be asked to complete a clinical exercise test conducted by a cardiologist.

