#### Manual dexterity

The Box and Block Test (BBT) [44] is a measure of gross manual dexterity consisting of a box divided by a partition into two equal-sized compartments and 100 2.5 cm square wooden blocks. The box will place on the side containing the blocks toward the tested hand. The task is to move the maximum number of wooden blocks, one at a time, across the partition in the middle of the box within 60 s. The hand must crossover the barrier to score one block. Multiple blocks carried over at the same time count as a single block. One practice trial will be performed before the assessment. The score recorded is the number of blocks that were moved for 60 s [44]; the average of three tests will be used to calculate the BBT score. The evaluation will be filmed with a camera placed at a standard position and distance; scoring will be confirmed by evaluation of the video recording.

The Nine-Hole Peg Test (NHPT) [45] assesses fine manual dexterity. The test consists of a nine-peg wooden board with nine holes and a container with nine pegs. The side with the pegs will be placed toward the affected upper limb, and the pegs are picked up and placed in the holes, one at a time, and then removed and placed back in the container [45]. If a peg is dropped, then the examiner quickly places it (or a replacement) in the container. One practice trial will be given before the assessment. The score is recorded as the time in seconds necessary to perform the test [46], and the total score will be calculated by the average of the three trials. The time taken to complete the examination will be recorded with a maximum time of 180 s [46]. If the person does not have enough skill to complete the test, then the pegs/s will be calculated using the number of pegs placed [49] compared to the time limit of 180 s. The evaluation will be filmed with a camera placed at a standard position and distance; scoring will be confirmed by evaluation of the video recording.

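### Baseline impairment (UE-FMA) is measured before allocation but enters no between-arm analysis, so the Mann-Whitney, single-visit and group-main-effect comparisons lose precision

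*Protocol article*

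**What the plan says.** The Study setting and recruitment section of the protocol article lists, among the screening assessments, "upper extremity sensorimotor impairment assessment using Fugl-Meyer Assessment (UE-FMA"). The score is therefore in hand for every participant before allocation.

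Under Randomization and blinding, "The randomization method will be matched by age and gender". Impairment is not an allocation factor.

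The Statistical analysis section gives UE-FMA one role: "Median, maximum and minimum values will be used to describe poststroke time and UE-FMA score". It then sets out two routes.

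- **Parametric:** a two-way repeated-measures ANOVA with group, evaluation time and their interaction. Baseline is one of the four levels of time.
- **Nonparametric:** Friedman and Wilcoxon tests within each group, and a Mann-Whitney test between groups at each visit with threshold 0.012.

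Neither route contains a covariate. Baseline values appear only as one of the visits.

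**The concern.** Impairment severity plausibly explains much of the spread in dexterity and motor function in chronic stroke. When a prognostic score measured before allocation is left out, its share of the outcome variance stays in the error of any comparison that does not remove it some other way. A chance severity difference between arms also passes into the estimate.

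This matters most on the nonparametric route, where the Mann-Whitney tests are the only between-arm tests and use neither the baseline outcome nor UE-FMA. That route is foreseeable for the Nine-Hole Peg Test (NHPT), on which the trial is sized, because it is a timed score with a ceiling: "The time taken to complete the examination will be recorded with a maximum time of 180 s".

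**Working it through.** **Inputs from the protocol article.** "The sample size was calculated with G*Power software using the independent t-test, 85% power, alpha 0.05, and 20% drop-out"; "a sample size of 78 individuals (39 per group) is required for this study". NHPT data from a cited study "were considered for this calculation", but no mean difference, SD or standardised effect is printed. The abstract gives a different total: "Sixty-two individuals with chronic hemiparesis will be randomized into two groups".

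**The plan's own figure.** Without an effect size, 78 cannot be reproduced forwards. Backwards, 31 per arm / (1 − 0.20) = 38.75, rounded up to 39 per arm, or 78. The abstract's 62 equals 2 × 31, the evaluable number. With 31 per arm and 85% power, the noncentral-t calculation implies d = 0.774 (two-sided; 0.689 if one-sided). I use 31 per arm and d = 0.774.

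**Assumed, because the documents give neither:** the correlation r of UE-FMA with the outcome, and the outcome's repeatability between visits.

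**1. Single-visit comparison, no other covariate.** Variance is multiplied by 1 − r²; the equivalent evaluable total is 62 / (1 − r²).

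| r | Variance cut | Equivalent total | Power, two-sided 0.05 | Power at 0.0125 |
|---|---|---|---|---|
| 0 | 0 | 62 | 85% | 68% |
| 0.3 | 9% | 68 | 88% | 73% |
| 0.5 | 25% | 83 | 93% | 82% |
| 0.6 | 36% | 97 | 96% | 89% |

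The last column uses a t-test approximation near the Mann-Whitney threshold (0.05/4 = 0.0125).

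**2. What the interaction and the outcome's own baseline already remove.** A simulation (4,000 replicates, 31 per arm, d = 0.77, r = 0.6) gave these standard errors (SE) of the arm difference. The second row lets less impaired people gain more, with the severity loading 0.2 higher after treatment.

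| Setting | Post visit only | Change (group-by-time) | Own baseline | Own baseline + UE-FMA |
|---|---|---|---|---|
| Repeatability 0.7, severity stable | 0.254 | 0.198 | 0.185 | 0.177 |
| Repeatability 0.7, severity predicts gain | 0.288 | 0.205 | 0.202 | 0.178 |

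The first row agrees with large-sample formulas: √(2/31) = 0.254 for post only; √(2(1 − 0.7) × 2/31) = 0.197 for change; √((1 − 0.7²) × 2/31) = 0.181 for own baseline. Estimating covariates with 62 people explains the slightly larger simulated values.

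Stable severity cancels in the change contrast. In the second row it does not cancel fully: 0.2² = 0.04 is added to the change variance of 0.60.

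**3. UE-FMA's own increment over the baseline outcome.**
- Stable severity: 1 − (0.177/0.185)² = 8%. Power in that setting is 97% for change, 98% with own baseline and 99% with both.
- Severity predicts gain: 1 − (0.178/0.202)² = 22%. If instead the more impaired gain more (loading 0.2 lower), own baseline alone gives 0.175 and adding UE-FMA leaves it at 0.175.
- A second simulation (3,000 runs per setting, retest correlation 0.85, r = 0.5 to 0.7, 0 to 40% of people at 180 s) gives 0 to 11% with stable severity and 18 to 26% if less impaired people gain more.
- A noisier outcome leaves more to gain: at repeatability 0.5 and r = 0.6, 1 − (0.204/0.222)² = 16%.

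**4. Chance imbalance.** The SD of the standardised UE-FMA difference is √(2/39) = 0.226 with 39 per arm and √(2/31) = 0.254 with 31. The chance of a difference above 0.3 SD is 18.5% or 23.8%; above 0.5 SD it is 2.7% or 4.9%. At r = 0.6, an imbalance of 0.3 SD moves a single-visit comparison by 0.6 × 0.3 = 0.18 SD.

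**The case against.** A reader might infer that severity spread stays in the error of every between-arm comparison and that imbalance goes wholly uncorrected. The documents do not support this. Baseline is a level of time in the ANOVA, so the group-by-time test works on within-person error and stable severity drops out. The 9%, 25% and 36% cuts therefore do not apply to that test.

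One might also argue that UE-FMA is needed because NHPT stops grading people at 180 s. The Manual dexterity section gives non-completers a pegs-per-second score, so they are still graded. The simulation with people piled at the cap ignores that rule, and the upper ends of its ranges may be too high for NHPT.

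Three further objections have weight:

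- Under randomisation the unadjusted tests keep their type I error, and chance imbalance is already in their sampling distribution. This stands: the point concerns precision and the estimate conditional on the imbalance that occurs.
- The outcome's own baseline is the stronger covariate. This stands too, but the plan does not use it as a covariate either.
- The choice could be left to a statistical analysis plan. This is weaker, because the article names the model, its factors, the fallback tests and their thresholds, and gives UE-FMA a stated role that excludes adjustment.

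**Conclusion.** The point holds with limited scope. UE-FMA enters neither the allocation nor any stated between-arm analysis. The Mann-Whitney tests, the group main effect and single-visit comparisons are unadjusted for severity; the interaction removes only its stable part.

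The loss is one of efficiency. Against a comparison with no covariate it is 9% to 36% of variance for r from 0.3 to 0.6. The larger share is recoverable from the outcome's own baseline: in the stable-severity setting, 1 − (0.185/0.254)² = 47% of the post-only variance. UE-FMA then adds about 0 to 11% at repeatability of 0.7 or more (16% in the one setting run at 0.5), or about 18 to 26% if less impaired people gain more. No passage establishes that last condition, and every correlation and repeatability is assumed.

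It would be wrong to infer a biased treatment effect or invalid tests. This is an improvement worth making before unblinded analysis, since adjusting after seeing an imbalance would be post hoc.

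**What to change.** Pre-specify the between-arm comparison of the 3-, 30- and 90-day visits as a baseline-adjusted model, either ANCOVA at each visit or a repeated-measures model of the three visits. Use two continuous covariates: the outcome's own baseline and UE-FMA. In the repeated-measures version give each a by-visit term. Adding a UE-FMA main effect to the present ANOVA would not help, because with baseline kept as a level of time it leaves the group-by-time test unchanged.

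On the nonparametric route, replace the unadjusted post-intervention Mann-Whitney tests with rank ANCOVA: regress the outcome ranks on the ranks of the same two covariates, both arms pooled, and compare the residuals between arms. Restate the Bonferroni thresholds for the revised set of comparisons. Keep the descriptive median and range.

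The data are already planned, so there is no added burden on participants. The cost is a short change to the analysis text and a few degrees of freedom: 2 per single-visit ANCOVA, or 2 covariates × 3 visits = 6 in the repeated-measures model.

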Considering a type of implicit learning, motor priming has been used in neurorehabilitation to facilitate motor learning [22, 26]. The priming theory presumes that when the brain is activated using an intervention delivered prior to the motor learning intervention, it will become more responsive to motor training due to increased neural activity. This “therapeutic window” may result from the modulation of long-term potentiation or long-term depression, such as mechanisms [22, 27, 28]. Movement-based priming, using repetitive or continuous, unilateral or bilateral movements, is an important method of priming the motor cortex in neurorehabilitation [22].

This protocol describes a single-blinded, randomized clinical trial designed to determine whether AE, as a form of movement-based priming, has an effect on the outcomes of m-CIMT, specifically the recovery of the skill of paretic upper limb in persons with chronic stroke. We hypothesize that AE will potentiate m-CIMT, resulting in improved manual dexterity in people in the chronic phase poststroke.

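### The ANOVA tests interaction, group and time without saying which answers the between-arm hypothesis, and the group main effect averages in the pre-treatment visit

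*Protocol article*

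**What the plan says.** The Background section of the protocol article states a between-arm hypothesis: "We hypothesize that AE will potentiate m-CIMT, resulting in improved manual dexterity in people in the chronic phase poststroke".

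The Statistical analysis section then sets out, for every dependent variable:

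- **Parametric branch.** A two-way repeated-measures ANOVA to "examine the effect of group-by-evaluation time interaction, group (AE + m-CIMT and Stretching + m-CIMT), and evaluation time (baseline, 3, 30 and 90 days" after treatment. Baseline is one of the four levels of time: "evaluation time (baseline, 3, 30 and 90 days after the intervention".
- **Multiplicity.** After Bonferroni correction, "each of the 10 planned comparisons will have to achieve" p = 0.005. The ten are not listed.
- **Effect estimate.** The pre-to-post mean difference and its 95% CI "will be calculated for each group (EA + m-CIMT and Stretching + m-CIMT) in order to estimate the effect of the intervention". Partial eta squared is the effect size, but it is tied to no ANOVA term.
- **Nonparametric branch.** Friedman and Wilcoxon tests within each arm, and a Mann-Whitney test at p < 0.012 "to compare the groups in each time evaluation". No test compares change between arms.

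The Sample size section says: "The sample size was calculated with G*Power software using the independent t-test, 85% power, alpha 0.05, and 20% drop-out". The result is 39 per group.

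**The concern.** Potentiation of m-CIMT means that one arm improves more than the other. Among the three ANOVA effects, only the group-by-time interaction tests a difference in change. The time effect will appear if m-CIMT works, whatever aerobic exercise does. The group main effect compares four-visit averages, one visit of which precedes treatment.

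The only estimate with a confidence interval is within-arm, so it contains the m-CIMT effect, practice and regression to the mean as well as any priming. Nothing stated commits to the between-arm contrast or to a visit. An analyst following this section could read a significant group or time effect as support, or read a non-significant group effect as absence of benefit when the interaction shows one.

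**Working it through.** **Inputs from the document.** 39 per group, 20% drop-out, 85% power, alpha 0.05; four visits; thresholds 0.005, 0.008 and 0.012.

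**The plan's own figures.** 39 × 0.8 = 31.2, so about 31 evaluable per arm; equally 62/0.8 = 77.5, rounded up to 78. The thresholds are 0.05/10 = 0.005, 0.05/6 = 0.0083 and 0.05/4 = 0.0125. The sample size itself cannot be reproduced, because the article gives no effect size or SD.

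**Assumptions.** An effect of δ = 0.774 SD, back-solved as the value giving 85% power in a two-sided t-test with 31 per arm (sidedness is not stated). Equal correlation ρ between visits, taken as 0.5 to 0.8. No missing data.

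**Dilution.** A lasting effect has visit profile (0, δ, δ, δ), and its four-visit mean is 3δ/4 = 0.5805. A day-3-only effect (0, δ, 0, 0) has mean δ/4 = 0.1935.

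**Power at 0.05.**
- Group: F(1, 60), noncentrality (31/2) × mean² / [(1 + 3ρ)/4].
- Interaction: F(3, 180), noncentrality (31/2) × Σ(δₜ − mean)² / (1 − ρ). For both profiles Σ = 0.75 × 0.774² = 0.449.
- With equal correlations the two tests are nearly independent, so P(different verdicts) ≈ P_G(1 − P_I) + P_I(1 − P_G).

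| Profile | ρ | Group | Interaction | Different verdicts |
|---|---|---|---|---|
| Lasting | 0.5 | 81% | 89% | 26% |
| Lasting | 0.7 | 72% | 99% | 28% |
| Lasting | 0.8 | 68% | about 100% | 32% |
| Day 3 only | 0.5 | 16% | 89% | 77% |
| Day 3 only | 0.8 | 13% | about 100% | 87% |

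Monte Carlo runs of the same 2 × 4 design agree to within about two percentage points. At 0.005 instead of 0.05, the lasting effect gives different verdicts in about 50 to 66% of trials.

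**Baseline imbalance.** With 31 per arm, the chance baseline difference has standard error √(2/31) = 0.25 SD. A difference b enters the group contrast as b/4 directly and, through the correlated later visits, as a further 3ρb/4. The total is b(1 + 3ρ)/4, or 0.625b to 0.85b. With no treatment effect but a stable 0.5 SD difference imposed at all four visits, group is significant in 56 to 68% of simulated trials and interaction in about 5%.

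**False positives if either omnibus test counts.** At 0.05: 1 − 0.95² = 9.75% (simulated 9.5 to 10.0%). At 0.005: 1 − 0.995² = 1.0%.

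**The case against.** Several stronger readings are tempting and are not supported.

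- **That the plan declares no effect decisive.** It is silent. A full protocol or SAP, not shown here, may name the decisive test. The interaction is listed first, and the hypothesis points to it. This stands. The point rests on what the section does state: a diluted group effect offered alongside the interaction, and a within-arm effect estimate.
- **That the false-positive rate is nearly doubled.** This holds only if both omnibus tests are read at 0.05. The 0.005 rule may cover them. Alternatively, the ten comparisons may be six visit pairs plus four between-arm comparisons, which would fit the 0.008 and 0.012 thresholds. That is inference, because the ten are not listed.
- **That the sample-size test matches none of the three effects.** In this design the group effect is a t-test on each participant's visit mean, so the form does match. What does not carry over is the power: an effect sized for 85% gives 68 to 81% on that mean.
- **That the tests contradict each other.** They test different null hypotheses. With no effect and no imbalance they differ in only 9 to 10% of trials. The highest rates need an effect confined to day 3.
- **That baseline imbalance inflates type I error.** Over repeated randomisations the group test keeps its 5% level. The 56 to 68% applies only to trials with the imposed imbalance, about two standard errors in size.
- **That every between-arm test here is flawed.** A Mann-Whitney test at a post-treatment visit is a valid comparison. However, the four-visit threshold suggests that one of the four is at baseline, and no deciding visit is named.

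**Conclusion.** The concern holds in limited form. As written, the section does not tie its analysis to the between-arm difference in change that the trial hypothesises. One of the effects it lists is a weak and noisy measure of that difference, and its stated estimate is within-arm.

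The practical size is a 26 to 32% chance of different verdicts from group and interaction under a lasting effect at 0.05. It rises if the effect fades. This rests on an assumed 0.774 SD effect, correlations of 0.5 to 0.8 and 31 evaluable per arm. The 3/4 and 1/4 dilution factors need none of these assumptions. The harm arises only if the group or time effect, or a within-arm difference, is read as the treatment effect; the text does not prevent that and does not say it will happen. The change should be made, but the point does not show the trial to be invalid.

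**What to change.** In the Statistical analysis section:

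1. State that the treatment effect is judged by the difference between arms in change from baseline at one visit, named in advance by the sponsor.
2. Report that difference with a 95% CI in place of the within-arm pre-post differences as the estimate of effect.
3. Label the group and time main effects descriptive and the other visits supportive.
4. In the nonparametric branch, use a Mann-Whitney test on change from baseline to the same visit.
5. List the ten comparisons and say whether this contrast is among them, so that its threshold is known.

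The contrast is itself a two-group t-test on change, with SD √(2(1 − ρ)). At 0.05 and δ = 0.774 its power is 85% at ρ = 0.5 and higher above that; below 0.5 it would fall short. Change scores do not wholly remove baseline imbalance: under the same assumptions a difference b shifts the contrast by −(1− ρ)b, or 0.5b to 0.2b in size, against 0.625b to 0.85b for the group effect.

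The cost is wording, plus giving up claims based on the group main effect or on another visit. No new data or participants are needed.

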### Primary outcome measures

#### Self-reported upper limb use

Motor Activity Log (MAL) [35–37] is a structured interview that evaluates the spontaneous use of the more affected upper limb. Each item independently asks about how much and how well the most affected upper limb is used in daily activities over the last week. A 6-point amount of use scale (score range, 0–5) quantifies how much the affected arms are used and a 6-point quality of movement scale (score range, 0–5) quantifies how well the affected arms are used [48]. Scores on this measure have adequate reliability and validity in individuals with stroke [35, 36].

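### The Bonferroni rule does not cover the four unranked primary scores, and its between-group threshold moves from 0.005 to 0.012 with pretest results

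*Protocol article*

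**What the plan says.** Under Primary outcome measures the protocol article places three instruments that yield four scores.

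- The MAL "is a structured interview that evaluates the spontaneous use of the more affected upper limb". It gives two separate 0–5 scales, because "Each item independently asks about how much and how well the most affected upper limb is used in daily activities over the last week".
- The BBT "is a measure of gross manual dexterity consisting of a box", and "the average of three tests will be used to calculate the BBT score".
- The NHPT measures fine dexterity, and "the total score will be calculated by the average of the three trials".

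None of the four is ranked, and no rule says which must succeed. The hypothesis in the Background concerns dexterity: aerobic exercise is expected to strengthen the therapy, "resulting in improved manual dexterity in people in the chronic phase poststroke". The Sample size section uses NHPT data alone, with alpha 0.05 and 85% power. It plans a recalculation on that same variable after five participants per group.

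The Statistical analysis section applies one procedure to every dependent variable. If the normality and homogeneity tests pass, a repeated-measures analysis of variance is used and each of 10 planned comparisons needs p = 0.005. Otherwise a Friedman test at 0.05 leads to Wilcoxon tests at 0.008 within each group, and Mann-Whitney tests at 0.012 compare the groups at each assessment. The reason given for the correction is "To protect against Type I error".

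**The concern.** A correction that is said to control type I error should state the set of tests over which it does so. Here each threshold looks right for one outcome, but it is then reused for every outcome, including four that are all called primary. The between-group threshold also depends on pretests run on the trial's own data, so the strictness of the treatment comparison is not known until the data are in. At stake is how a reader should weigh a single significant between-group result among four primary scores and three follow-up visits, when the stated protection does not extend to that set.

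**Working it through.** **Reproducing the plan's thresholds.**

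- 0.05 / 10 = 0.005, as stated.
- Four assessments give 4 × 3 / 2 = 6 time pairs; 0.05 / 6 = 0.0083, stated as 0.008.
- Four assessments give four group comparisons; 0.05 / 4 = 0.0125, stated as 0.012.

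The last two are cut downwards, so they are slightly conservative. The arithmetic is sound for each family taken alone.

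**What the divisors cover.** The article does not list the 10 comparisons. Reading them as 6 time pairs plus 4 group comparisons (6 + 4 = 10) is an inference, supported by the 6 and 4 of the other branch. In any case 10 is too few for four scores at four assessments (4 × 4 = 16).

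**Within one outcome, between groups.** The sums are 4 × 0.005 = 0.020 and 4 × 0.012 = 0.048. Both are under 0.05, so the rule holds there.

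**Across the primary scores.** Only post-treatment group comparisons can show a treatment effect: 4 scores × 3 visits = 12 tests. The ceiling is 12 × threshold. If the tests are independent, the familywise error is 1 − (1 − threshold)^12.

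| Branch | Threshold | Ceiling | If independent |
|---|---|---|---|
| Parametric | 0.005 | 12 × 0.005 = 6.0% | 1 − 0.995^12 = 5.8% |
| Non-parametric | 0.012 | 12 × 0.012 = 14.4% | 1 − 0.988^12 = 13.5% |

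**Effect of correlation.** The article gives no correlations. I assumed 0 to 0.7 between scores and 0.5 or 0.8 between visits, and simulated correlated normal test statistics (200,000 replicates per setting). The familywise error was 3.4% to 5.5% at 0.005 and 7.4% to 12.5% at 0.012.

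**Counting MAL once.** Three measures give 9 tests. The parametric ceiling is 9 × 0.005 = 4.5% (4.4% if independent). The non-parametric ceiling is 9 × 0.012 = 10.8% (10.3% if independent).

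**The switch.** 0.012 / 0.005 = 2.4, so failing a pretest relaxes the between-group threshold 2.4-fold.

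**The case against.** The best reply is that a hierarchy across outcomes is often left to a full protocol or analysis plan, and neither is shown. This is fair as far as silence goes. But the article does fix thresholds, applies them to all variables and claims a property for them, and the pretest-dependent threshold is part of the rule as written.

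A second reply is that, on the parametric branch, treatment comparisons barely exceed 5% and may fall below it. That stands, and it limits the conclusion.

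Several stronger readings are tempting, but the text does not support them.

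- **About 20% over 40 comparisons (40 × 0.005).** This needs the unlisted family of 10. On the inferred reading, 24 of the 40 are changes over time and 4 are baseline contrasts. Only 12 bear on the treatment effect.
- **About 18.5% from four interaction tests at 0.05.** The article states no alpha for the interaction.
- **About 14% within one outcome on the non-parametric branch (12 × 0.008 + 4 × 0.012 = 0.144).** This ignores the Friedman test that precedes the Wilcoxon tests, and 0.096 of it is within-group. It should not be confused with the 14.4% above, which is between groups across four scores.
- **Any one significant score makes the trial positive.** No such success rule is stated, and the hypothesis is about dexterity, so MAL alone would not confirm it.
- **Participants could guess their arm, which would affect a self-reported primary.** Whatever its merit, this is a separate matter of blinding and has no bearing on multiplicity.

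**Conclusion.** The point holds in limited form. The rule controls between-group error within an outcome, but not across the four scores called primary, and its between-group threshold depends on the data. The ceiling is 6% on the parametric branch, a negligible excess that disappears if MAL is counted once or correlation is strong. It is 14.4% on the non-parametric branch, where the error stayed above 5% under every correlation assumed. If pretests send some scores down each branch, the ceiling lies between the two.

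These figures rest on counting the two MAL scales separately, excluding baseline, treating the branch as given, and taking each test to be exact at its stated level. That the divisors are per outcome is an inference from their values.

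**What to change.** - Name NHPT as the single primary outcome. It is a dexterity measure and the one behind the sample size.
- Specify one between-group comparison at one post-treatment visit, tested at the design alpha of 0.05. The text gives no basis for preferring a particular visit. The sponsor should choose it before any by-group data are seen, including at the planned look after five participants per group.
- Fix the test for that comparison in advance, and use one between-group threshold whatever the normality result. The choice must suit an NHPT score recorded in seconds for completers and pegs per second for others, so a common scale has to be settled first.
- Make BBT, MAL and the other visits secondary, tested in fixed order or by Holm.

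The cost is an amendment to the protocol, and to the registry entry (not seen here) if it lists the same primaries. BBT and MAL could then no longer carry the trial alone.

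There is also a gain. The 39 per group matches 31 evaluable (31 / 0.8 = 38.75, rounded up). The article gives no effect size. With 31 per group, 85% power and an assumed two-sided 0.05, the implied standardised difference is 0.77. At that difference, t-test power is 85% at 0.05 but 56% at 0.005, so a single primary comparison restores the power the trial was sized for.
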